### Study Timeline and Data Collection

#### Objective 1: Effectiveness of 3MDR

Data will be collected from intervention and control group participants at initial assessment (T0), prior to delivery of 3MDR (T1), pre/post 3MDR sessions (T2.1-2.6), and at 1 week (T3), 1 month (T4), 3 months (T5), and 6 months (T6) postintervention (Figure 3).

**Figure 3 figure3:**
[figure not shown]
Multimodular motion-assisted memory desensitization and reconsolidation (3MDR) data collection time points for the intervention (treatment; blue/red) and waitlist control (green) groups. The syringe icon denotes blood collection and the square icon denotes saliva collection.

Clinical outcome measures will be collected at each time point using the questionnaires listed in Table 1. Qualitative interviews will occur at T3 through T6. Physiological, biometric, and qualitative audio/video data will be collected at T2.1-T2.6. Blood and saliva samples will be collected at baseline (T1), before (pre) and immediately after (post) 3MDR sessions at T2.1 and T2.6, post 3MDR sessions at T2.3 and T2.4, at 1-week follow up (T3), and at 1-, 3-, and 6-month follow ups (T4, T5, T6) for the analyses of peripheral blood and salivary biomarkers, including inflammatory mediators, neuroendocrine hormones, and microRNAs (see Multimedia Appendix 1).

Demographic information will include gender, age, ethnicity, marital status, military branch (ie, army, navy, or air force), and occupation. Psychological outcomes will be assessed through paper-based questionnaires administered during each contact with participants (Table 1). For further information on each outcome measure, refer to Multimedia Appendix 2.

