The main research questions to be addressed include: (1) Will participants’ combat-related TR-PTSD and moral injury symptoms, and associated behavior and physiology, change after an intervention of 3DMR therapy compared with treatment as usual? (2) Will peripheral multiomic biomarkers related to traumatic stress (ie, blood and salivary proteomic and genomic profiles of neuroendocrine, immune-inflammatory responses, and microRNA) be modified by the 3MDR intervention and show utility for predicting patient outcomes posttreatment? (3) What are the 3MDR clinicians’, operators’, and participants’ perceived technology acceptance and usability of 3MDR on the CAREN system? (4) What is the overall participant experience of the 3MDR intervention and comparability to PTSD therapies that the participants had previously engaged in? (5) Will 3MDR clinicians and operators experience perceived or secondary traumatic stress, or a change in their professional quality of life as a result of delivering 3MDR?

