### Specific Objectives

The first objective of the study is to examine the effect of 3MDR therapy on combat-related TR-PTSD and moral injury symptoms, behaviors, and physiological measures for CAF-SMs and veterans who have not benefited from other trauma therapies. The second objective is to examine the perceived technological acceptance and usability of 3MDR by CAF-SMs and veterans with combat-related TR-PTSD as well as 3MDR clinicians and operators. The third objective is to examine the effects of 3MDR on the operators and clinicians who provide this intervention to military members and veterans with combat-related TR-PTSD. In addition to conventional statistical analyses, the final objective of this study is to explore the application of machine learning in an attempt to identify individual data patterns that may predict diagnosis, severity, and potential treatment outcomes.

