##### Physiological Data

Walking and eye-scanning patterns, as well as physiological data (eg, heart rate, breathing rate, gait pattern, force plate analysis) will be collected during the training session through the CAREN system, Tobii Mobile eye-tracking glasses, Muse electroencephalogram (EEG), and Zephyr BioHarness 3.

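### Research question 1 sets physiology against treatment as usual, but the CAREN and wearable recordings are scheduled only at 3MDR sessions, so controls have none during the randomised comparison

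*Protocol article*

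**What the plan says.** In the protocol article, Overall Aims, the first main research question covers symptoms "and associated behavior and physiology, change after an intervention of 3DMR therapy compared with treatment as usual". Specific Objectives, in its first objective, refers to the "effect of 3MDR therapy on combat-related TR-PTSD and moral injury symptoms, behaviors, and physiological measures" and names no comparator.

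The measurements are described under Study Timeline and Data Collection. The Physiological Data subsection lists "Walking and eye-scanning patterns, as well as physiological data (eg, heart rate, breathing rate, gait pattern, force plate analysis" and similar signals, which "will be collected during the training session through the CAREN system", together with eye-tracking glasses, a portable EEG and a chest-worn monitor. The text under Figure 3 fixes the time points: "Physiological, biometric, and qualitative audio/video data will be collected at T2.1-T2.6". The Objective 1 timeline sets out the visits as "prior to delivery of 3MDR (T1), pre/post 3MDR sessions (T2.1-2.6), and at 1 week (T3"; T2.1 to T2.6 are thus the six therapy sessions.

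Study Design and Setting, and Recruitment, say that the 20 waitlist participants have 9 weeks of usual treatment first and are then offered 3MDR.

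**The concern.** A question worded as 3MDR against usual treatment needs the measure in both arms, at least at the end of the randomised period. If physiology is recorded only while someone is receiving 3MDR, the control arm contributes nothing to that comparison. What remains is change over the course of treatment. A fall in heart rate or a steadier gait from the first to the last session could reflect benefit. It could equally reflect getting used to the room, practice on the treadmill, seeing the same kind of image repeatedly, or the passage of weeks.

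This matters because the item sits in the first main research question, and because Projected Outcomes in the Discussion expects the eye-tracking and EEG data to shed light on how 3MDR works. An uncontrolled change placed under a controlled question invites a causal reading that the data cannot carry.

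**Working it through.** No formula applies and the plan gives no figure to reproduce. The check sets the schedule against the comparison asked for.

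1. **Comparison required.** Research question 1: change in physiology after 3MDR versus usual treatment. The randomised period runs from baseline (week 1) to week 9.

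2. **When these signals are recorded.** The text under Figure 3 gives T2.1 to T2.6, that is, 6 session time points. The same paragraph gives blood and saliva a separate and wider schedule: T1, selected sessions, and T3 to T6. So the article distinguishes the two kinds of data and ties physiology to the sessions. Table 1 has no row for physiology.

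3. **Who has those sessions in the randomised period.**
   - Immediate arm: 20 participants × 6 sessions = 120 scheduled session recordings, if all sessions are attended.
   - Waitlist arm under usual treatment: 20 participants × 0 sessions = 0.
   - A control reaches T2.1 only after the 9 weeks, and only by accepting crossover. By then that person is receiving 3MDR.

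4. **What that leaves.** The scheduled data support a within-person change from T2.1 to T2.6. They contain no change under usual treatment to subtract from it.

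5. **What is not affected.** Table 1 schedules these in both arms:
   - CAPS-5, SUDS and BrainFX at week 1 and week 9.
   - PCL-5, PABQ, MISS-M, GAD-7, PHQ-9, PDEQ, AUDIT, DERS-18, CD RISC-25, OQ-45 and EQ-5D/EQ VAS at week 9. For these, controls have no baseline entry.

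   The first set supports a baseline-adjusted comparison. The second supports a randomised comparison of week 9 values. Blood and saliva markers belong to research question 2 and are outside this point.

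6. **Passages that might supply a control recording.**
   - The Objective 1 timeline says data come from both groups. A control's T2 data can arise only during 3MDR.
   - Objective 4 (machine learning) refers to physiological and other data from T0 to T3. This is one input window for several data types and names no recording under usual treatment.
   - The training session in Physiological Data could mean the introductory session. Recruitment describes that as a CAREN session for intervention participants, so at most it adds a pre-treatment recording for people about to receive 3MDR.
   - Figure 3 is not shown. Its caption mentions icons for blood and saliva only.

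None of these puts a recording in a control during usual treatment.

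**The case against.** The strongest reply is that this is one clause in one research question. The primary aim and Hypothesis 1 name usual treatment for symptoms only (the aim adds moral injury), and the sample size rests on clinician-rated PTSD symptoms. The analysis section specifies mixed models for psychological outcomes, and the use it describes for physiological data is exploratory prediction. No passage plans to test session 1 against session 6 and call the result a difference from usual treatment. All of this is correct. It limits the weight of the point but does not supply the missing control data.

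Some stronger readings are tempting and should not be made:

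- A reader might infer that the first objective also promises a controlled effect on physiology. It does not; it names no comparator.
- A reader might infer that behaviour as a whole has no control data. The research question says behaviour, not walking. Avoidance behaviour has a questionnaire, the PABQ, taken in both arms at week 9 and covered by the planned mixed models. Only the walking, gait and eye-scanning recordings share the gap.
- A reader might infer that only CAPS-5, SUDS and BrainFX can be compared with usual treatment, because only they have a baseline in both arms. Randomisation makes a week 9 comparison valid without a control baseline, though less precise.
- A reader might infer that no physiology at all is recorded outside sessions in either arm. The T0 to T3 wording and the ambiguous training session leave that open. The firm statement is that none is scheduled under usual treatment.

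**Conclusion.** The point holds for the CAREN and wearable recordings. As scheduled, the comparison with usual treatment that research question 1 asks for cannot be made for them: none of the 20 controls has a scheduled recording in the 9-week randomised period. The T2.1 to T2.6 change is uncontrolled.

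The primary CAPS-5 comparison is untouched, as are the week 9 comparisons of the questionnaires. This should be corrected because it changes what the trial can conclude about physiology, but it does not threaten the main result.

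The conclusion assumes that the article's text states the schedule completely and that the missing figure adds no control recording. The T0 to T3 wording under Objective 4 sits loosely with the session-only schedule and needs reconciling either way.

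**What to change.** 1. In research question 1, remove the comparison with usual treatment for the CAREN and wearable physiology. State that these are exploratory, uncontrolled changes within the course of treatment, from T2.1 to T2.6.
2. Keep the comparison with usual treatment for every measure taken in both arms at week 9. CAPS-5, SUDS and BrainFX have a baseline in both arms. PCL-5, PABQ, MISS-M and the other questionnaires are compared between arms at week 9.
3. In the first objective, add only that session physiology is uncontrolled.
4. As a partial control from data already collected, compare T2.1 recordings between the immediate arm and crossed-over controls, using pre-session values where available. Report this next to the T2.1 to T2.6 change. It gives some indication of how far the signals shift over 9 weeks of usual treatment. Two cautions belong with it: only controls who accept crossover contribute, and recordings made during session 1 are not free of 3MDR exposure.
5. Reconcile the T0 to T3 data window under Objective 4 with the session-only schedule, and say which session the training session is.

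The cost is a few changes of wording, one extra descriptive comparison and a narrower claim for physiology. No new visits, participants or equipment are needed.

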##### Physiological Data

Walking and eye-scanning patterns, as well as physiological data (eg, heart rate, breathing rate, gait pattern, force plate analysis) will be collected during the training session through the CAREN system, Tobii Mobile eye-tracking glasses, Muse electroencephalogram (EEG), and Zephyr BioHarness 3.

##### Subjective Measures

Video recording of each session will capture qualitative data of the exchange between the clinician and participant during the 3MDR session. Audio recordings of the therapeutic debriefs will also occur, during which the clinician and patient will discuss the experience of any remarkable or meaningful aspects of the session. The clinician will also share observations. Upon completion of the 3MDR intervention, audio-recorded iterative semistructured interviews will be conducted with all participants at week 10, and 1, 3, and 6 months postintervention to explore their experience of 3MDR, its impact on their PTSD symptoms and overall function, and participation in the research study.

#### Objective 2: Measure of Technology Acceptance and Usability

To measure the perceived technology acceptance and usability of 3MDR and the CAREN, two 15-question surveys based on the Unified Theory of Acceptance and Usability of Technology (UTAUT) model [56] will be administered pre/post exposure to CAREN and 3MDR. The surveys utilized Likert scores ranging from 15 to 105 points, with high scores indicating increased perceived technology acceptance and usability.

#### Objective 3: 3MDR Operators and Clinicians

The impact of delivering 3MDR will be examined with clinicians and operators using questionnaires related to technological acceptance, perceived stress, and professional quality of life prior to 3MDR training and on completion of a full course of 3MDR with a study participant (Table 2).

**Table 2 table2:** Time points of data collection for multimodular motion-assisted memory desensitization and reconsolidation (3MDR) clinicians and operators.

Construct to be measured	Measure	Week 1 (Baseline)	Week 9 (Post)
Technology Acceptance and Usability	UTAUT^a^ Questionnaire	X	X
Perceived Stress	PSS^b^	X	X
	SUDS^c^	X	X
	Subjective Interview		X
Professional Quality of Life	PQoL^d^	X	X
Secondary Stress	STSS^e^	X	X

^a^UTAUT: Unified Theory of Acceptance and Usability of Technology.

^b^PSS: Perceived Stress Scale.

^c^SUDS: Subjective Units of Distress Scale.

^d^PQoL: Professional Quality of Life Scale.

^e^STSS: Secondary Traumatic Stress Scale.

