**Methods:**

This is a mixed-methods waitlist controlled crossover design randomized controlled trial. Participants include both CAF-SMs and veterans (N=40) aged 18-60 years with combat-related TR-PTSD (unsuccessful experience of at least 2 evidence-based trauma treatments). Participants will also include clinicians and operators (N=12) who have been trained in 3MDR and subsequently utilized this intervention with patients. CAF-SMs and veterans will receive 6 weekly 90-minute 3MDR sessions. Quantitative and qualitative data will be collected at baseline and at 1, 3, and 6 months postintervention. Quantitative data collection will include multiomic biomarkers (ie, blood and salivary proteomic and genomic profiles of neuroendocrine, immune-inflammatory mediators, and microRNA), eye tracking, electroencephalography, and physiological data. Data from outcome measures will capture self-reported symptoms of PTSD, moral injury, resilience, and technology acceptance and usability. Qualitative data will be collected from audiovisual recordings of 3MDR sessions and semistructured interviews. Data analysis will include univariate and multivariate approaches, and thematic analysis of treatment sessions and interviews. Machine learning analysis will be included to develop models for the prediction of diagnosis, symptom severity, and treatment outcomes.

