Recruitment of 3MDR clinicians and operators (N=12) will be conducted through word of mouth among the six international 3MDR research teams located in the Netherlands, the United States (California and Maryland), the United Kingdom (Wales), and Canada (Alberta and Ontario). Clinicians and operators who have received training for 3MDR and completed 6 weeks of interventions will be eligible for a pre/post evaluation. Voluntary written informed consent will be obtained from all participants.

The control group will undergo screening for eligibility and baseline assessment, followed by 9 weeks of treatment as usual while the intervention group receives the 3MDR intervention. They will then be provided an opportunity to cross over into the intervention group.

For the introductory session, intervention group participants will become accustomed to the CAREN system by practicing the process associated with 3MDR, including walking on the treadmill while looking at a neutral image as the clinician guides them through the 3MDR protocol. The participant will be asked to provide (1) images reminiscent of the traumatic deployment event that preceded a PTSD diagnosis, ranked according to the emotional distress that each elicits (ie, from least to greatest level of distress); and (2) digital music tracks of a song that reminds them of their deployment and other sounds or music that provide positive feelings. A secondary purpose of this introductory session is also to transfer trust from their service provider to the 3MDR researchers and clinicians. One week after the introductory session, the 3MDR therapy will be initiated and participants will undergo 6 90-minute sessions.

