#### Objective 3: 3MDR Operators and Clinicians

Owing to the small anticipated sample size, nonparametric statistical analysis with the Wilcoxon signed-rank test will be employed to assess the outcome measures addressing clinician and operator stress. Qualitative interviews will be thematically analyzed as described above.

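### Clinician and operator pre/post timing conflicts with who is recruited, so the number of valid pairs for the staff stress test is undetermined

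*Protocol article*

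**What the plan says.** The protocol article describes the staff sub-study in several places.

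- **Timing** (Study Timeline and Data Collection, Objective 3): questionnaires are given "prior to 3MDR training and on completion of a full course of 3MDR with a study participant". Table 2 labels the two occasions Week 1 (baseline) and Week 9 (post). It does not link Week 1 to training or to first delivery.
- **Eligibility** (Recruitment): "Clinicians and operators who have received training for 3MDR and completed 6 weeks of interventions will be eligible for a pre/post evaluation".
- **Population** (abstract, Methods): "clinicians and operators (N=12) who have been trained in 3MDR and subsequently utilized this intervention with patients".
- **Source** (Recruitment): "word of mouth among the six international 3MDR research teams", with sites in the Netherlands, California, Maryland, Wales, Alberta and Ontario.
- **Analysis** (Data Analysis, Objective 3): "nonparametric statistical analysis with the Wilcoxon signed-rank test will be employed to assess the outcome measures addressing clinician and operator stress".
- **Hypothesis 3**: delivering 3MDR will not harm the mental health of staff in a way that affects their daily functioning.
- **Progress** (Results): 5 clinicians and 4 operators have completed either the pre/post measures or the interview.

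**The concern.** The signed-rank test works on within-person differences, so each person must have both scores, taken at the defined moments. Both moments conflict with the description of who enters.

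The pre score belongs before training, but the eligibility rule and the abstract describe people who are past training and past a period of delivery. The post score belongs after a course with a participant of this study, but staff are sought from teams in four countries. The patients are recruited through Canadian military, clinic, veteran and local community channels and treated in a hospital CAREN setting.

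What is at stake is the conclusion on staff safety. Hypothesis 3 predicts no harm, so two failures would both tend to look like confirmation: too few pairs to detect a change, or a baseline that already contains some effect of delivery.

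**Working it through.** **1. The pre score.** Objective 3 places it before training. Recruitment confers eligibility after training and 6 weeks of interventions. If enrolment starts at eligibility, a prospective pre-training score is no longer possible. If enrolment starts earlier and the Recruitment sentence only says who is evaluable at the end, the score is possible. The article does not say which applies.

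**2. The post score.** Objective 3 requires a course with a study participant. No section says that staff of the overseas teams treat this trial's participants, and no section provides a different post definition for them.

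**3. Number of pairs.** The article gives no sample-size calculation for the 12 staff, so there is no stated figure to reproduce; the G*Power calculation concerns patients only. The bounds are:

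- all 12 measured before training and followed through a qualifying course: 12 pairs;
- all 12 enrolled after training and delivery: 0 pairs.

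The Results section does not narrow this. It counts 5 + 4 = 9 people, but joins the pre/post measures and the interview with *or*, so the number of complete pairs among the 9 is unknown.

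**4. What the test can show.** For n pairs with non-zero differences and no ties, the smallest two-sided exact P arises when all differences have the same sign: P = 2/2^n.

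| Pairs | Smallest P |
|---|---|
| 4 | 2/16 = 0.125 |
| 5 | 2/32 = 0.0625 |
| 6 | 2/64 = 0.031 |
| 9 | 2/512 = 0.0039 |
| 12 | 2/4096 = 0.0005 |

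The two-tailed .05 level is stated under Objective 1 and is assumed to apply here. With 5 or fewer pairs the exact test cannot reject even if every person worsens. That point is reached once 12 − 5 = 7 of the 12 lack a valid pair.

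**5. Power.** Exact two-sided test at .05, 4000 simulated samples per cell, normal paired differences. The standardized effects are assumed; the article gives none.

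| Pairs | Effect 0.5 | Effect 0.8 | Effect 1.0 |
|---|---|---|---|
| 12 | 0.31 | 0.67 | 0.85 |
| 9 | 0.22 | 0.49 | 0.68 |
| 6 | 0.11 | 0.24 | 0.35 |
| 5 | 0 | 0 | 0 |

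Six pairs make rejection possible, but not likely.

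**6. A late baseline.** Let the true pre-training score be B, the lasting rise from delivery before the first questionnaire be s, and the later rise be t. The intended change is (B + s + t) − B = s + t. The change measured from the late baseline is (B + s + t) − (B + s) = t. If s is positive, the change is understated by s. If earlier delivery left no lasting rise, s = 0 and there is no bias. The article has no data on s.

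**The case against.** The best defence is that the Recruitment sentence is an evaluability rule: staff are measured before training, and only those who go on to complete training and a 6-week course count in the pre/post evaluation. On that reading it marks the same two moments as Objective 3, and the abstract merely describes people at the end of the process. The Results section suggests that some pre/post measures may already have been collected. The reference to a study participant could be loose wording in a condensed article, since the Discussion describes shared training, manual and fidelity checklists across the international studies.

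The evaluability reading is possible, but no section states it, and it does not settle whether a course delivered at an overseas site counts as post.

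The defence does rule out several stronger readings that a reader might infer:

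- That most of the 12 cannot supply a pair, or that no change score exists. The article gives no count of staff enrolled before and after training.
- That only 2 to 4 staff could qualify, on the basis of 12 staff spread evenly over six teams. Recruitment is by word of mouth, and nothing implies an even spread.
- That the change is certainly biased toward zero. This requires a lasting rise in stress from earlier delivery.
- That the technology acceptance score (UTAUT) is part of the Wilcoxon analysis. Data Analysis assigns that test to the stress measures and covers UTAUT separately under Objective 2.

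**Conclusion.** The point holds as an internal contradiction. Objective 3, Recruitment and the abstract disagree on when staff enter relative to training, the study-participant condition does not fit international recruitment, and Table 2 does not resolve either. The consequence is an undetermined number of valid pairs, between 0 and 12, rather than a demonstrated loss of most of them.

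The inability to reach P<.05 with 5 or fewer pairs rests on two assumptions: that the .05 two-tailed level carries over from Objective 1, and that the exact form of the test is used, which the article does not specify. Understatement of the change is a conditional risk. The sub-study is small, includes interviews and does not touch the primary patient outcome, but it is the basis for the trial's statement on staff safety.

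**What to change.** 1. Give one definition in the abstract, Recruitment, Objective 3 and Table 2 of when staff enter relative to training, and of which course sets the post score, including for staff of the overseas teams.
2. Include in the paired Wilcoxon analysis of the stress measures only staff whose baseline was completed before their training. Apply the same restriction to any clinician or operator UTAUT change, under its own analysis.
3. Report already-trained staff separately, as post-only, descriptive and interview data without a change score.
4. State the number of pairs with each result.
5. Do not cite a non-significant test with fewer than 6 pairs as support for Hypothesis 3.

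The cost is rewording and a smaller stated paired sample; no extra staff or procedures are needed. Up to 9 of the 12 may already have been assessed, and new wording cannot recover baselines that were not taken. For those people the change governs only how their data are classified and reported.
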